## 7.4 Exclusion Criteria

Patients must be excluded from participating in this study if they meet any of the following criteria:

- The patient has another confirmed condition that can fully account for the cognitive impairment, including but not limited to psychiatric disorders (schizophrenia, mood disorders, bipolar disorder and personality disorders); neuroinflammatory, neuroinfective, or neurodegenerative diseases; multiple sclerosis; genetic disorders; HIV; brain injuries; neurosurgery aftereffects, delirium). Patients with long-known, stabilized psychiatric or other brain conditions that cannot fully account for the cognitive impairment may be included in the study.
- The patient comes to observation for reasons other than diagnosis (disability assessment for social aids, cognitive assessment for driving license, etc.)
- The patient had a previous A $\beta$  imaging scan and/or has had other AD biomarker workup (fluorodeoxyglucose [FDG]-PET and/or cerebrospinal fluid [CSF] analysis) prior to screening. In some centres, the patient may receive a diagnostic workup before screening. These patients can be enrolled if the investigator is blind to the results until after randomization.
- The patient has a life-threatening unstable medical disease or psychiatric condition that could lead to difficulty in complying with the protocol.
- The patient is currently receiving an investigational pharmaceutical product or has participated in a clinical trial with an investigational pharmaceutical product within 30 days prior to screening, and/or was administered a radiopharmaceutical within 10 radioactive half-lives prior to study drug administration in this study.
- The patient is a woman who is pregnant, planning to become pregnant, or lactating. Pregnancy status of a woman with childbearing potential will be carried out before the PET scan. A woman is considered of childbearing potential (WOCBP), i.e. fertile, following menarche and until becoming post-menopausal unless permanently sterile ([www.hma.eu/ctfg.html](http://www.hma.eu/ctfg.html), Recommendations related to contraception and pregnancy testing in clinical trials, September 2014).
- The patient is not affiliated to the Social security and does not receive the rights and corresponding coverage, in accordance with the Code of Public Health.

- The patient is employed at the research department or memory clinic, it is directly involved with the study, and it is a family relative from any department personnel (i.e. partner, older child, sibling, biological or legal representative).
- Any of the contraindications as registered for the study drug used is applicable to the subject. Any of the warnings or precautions as registered for the IMP used is applicable to the subject, unless a risk-benefit assessment is favorable as per the judgement of the sponsor.

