### 5.3 Rationale for Conducting the Study

Brain amyloidosis is one of the two key pathophysiological events of Alzheimer's disease. Amyloid PET imaging has demonstrated good analytical validity in pathologically confirmed studies, i.e. high sensitivity and specificity towards moderate or frequent amyloid plaques. However, despite effectively representing "in vivo neuropathology", its clinical utility is unclear.

AMYPAD will study in a real-life setting to what extent amyloid PET imaging affects diagnostic confidence, patient management, and ultimately the cost-effectiveness of dementia care. The dementia field has been moving from a syndromic diagnosis (e.g. "dementia") to an etiologic diagnosis (e.g. "dementia due to Alzheimer's pathology", "dementia due to Lewy body pathology", etc.). AMYPAD relies on the assumption that a more accurate etiologic diagnosis is associated with better patient care, treatment, and outcomes. The etiologic diagnosis of AD requires the detection of the two key pathophysiological phenomena of the disease, i.e. deposits of amyloid and hyper-phosphorylated tau proteins in the brain. The ascertainment of brain amyloid can rely on PET with appropriate ligands or CSF assays of A $\beta$ 42.

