#### 5.4.1 Primary objectives

To test the hypothesis that the proportion of participants for whom the managing physician reaches an etiologic diagnosis with very high confidence ( $\geq 90\%$ ) at 12 weeks after baseline is higher for participants who underwent amyloid PET imaging shortly after baseline than for participants who have not yet undergone amyloid PET imaging (ie, participants scheduled to undergo amyloid PET imaging at 8 months [ $\pm 8$  weeks] after baseline).

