### 7.3 Inclusion Criteria

To be enrolled in the study, participants must meet all of the following criteria:

- The patient can be of any sex, gender, race, or ethnicity.
- SCD-Plus patients must be 60 to 85 years of age.
- Patients with MCI or with dementia must be 50 to 85 years of age.
- The patient must have a complaint (reported by the patient or by a caregiver) of cognitive problems that are considered by the managing physician to be possibly due to AD.
  - The patient must be entering a diagnostic assessment for the cognitive complaint.
  - The managing physician must feel that knowledge of the patient's brain amyloid status may increase diagnostic confidence and alter diagnosis and management.
  - Patients should not have known amyloid status prior to randomization.
- The patient must satisfy the diagnostic criteria for one of the following:
  - SCD-Plus (see Section 7.5.1)
  - MCI (see Section 7.5.2)
  - Dementia, where AD is in the differential diagnosis (see Section 7.5.3)
- The patient has undergone a dementia blood workup or will have one before amyloid PET.
- The patient has an MRI and/or CT scan (not older than 12 months) or will undergo one before amyloid PET.
- The patient can complete all clinical visits according to the protocol.
- The patient can tolerate a 20-minute amyloid PET scan.
- The patient (or, in case the patient is incapable of giving informed consent, next of kin or a legal representative as per national requirements) provides informed consent for study participation and data source verification. In case of a change in the capacity to consent, the local regulations will be applied. In case the patient is randomized to the Early Amyloid

PET arm, a new informed consent should be signed before the optional second imaging session.

- If the patient has dementia, a study partner is available for the duration of the protocol.
- In countries where patients unable of giving informed consent cannot be included in the study and an assessment of the patients' capacity to consent is requested, a study physician will assess the capacity to consent in patients with verifiable cognitive impairment prior to enrolment and regularly in the course of the study. If there are any doubts as to the patients' capacity to consent, the capacity to consent will be conclusively assessed by a specialist. Patients who are unable of giving informed consent, are excluded from the study in these countries.

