## 9.2 Baseline Visit (V0 at T0)

The baseline visit must occur within 14 days after the screening visit. The screening visit can be combined with the baseline visit.

At the Baseline Visit (Visit 0 [V0] at Time 0 [T0]), the participants/study partners will receive a diary/questionnaire. At the Baseline visit, the results of the following will be recorded for all participants:

- Mini-Mental State Examination (MMSE®)
- EQ5D-5L (EuroQoL 5-dimension questionnaire)
- ICECAP-O (ICEpop CAPability measure for Older people)
- Brief COPE – Brief Coping Orientation to the Problems Experienced)
- Hospital Anxiety and Depression Scale (HADS)
- Managing physician's syndromic diagnosis (SCD-Plus, MCI, or dementia where Alzheimer's Disease is in the differential diagnosis)
- Maximum 4 hypotheses of etiologic diagnosis made by the managing physician, each with a diagnostic confidence (only if the diagnostic confidence >90% is not achieved for one etiologic diagnosis hypothesis)
- Diagnostic confidence (the managing physician's confidence that the diagnosis is correct) for each hypothesis.
- The managing physician's estimate of the likelihood that the patient's symptoms are due to AD.

Results of an already available neuropsychological assessment can be used at Baseline visit only if the results are not older than 6 months and based on the managing physician clinical judgement that there are no reasons to expect a change in that period.

The participants will be stratified according to the syndromic diagnosis made by the managing physician and then randomised, as described in Section [8.3.2](#).

For participants in the Early Amyloid PET arm, amyloid PET imaging will be scheduled to take place within 4 weeks after baseline. Amyloid PET will be carried out with high priority for early amyloid PET arm patients.

For participants in the Late Amyloid PET and Free Choice arm, if results of any of the following tests are available at this visit, the results will be reviewed with the participant/study partner and recorded in the eCRF:

- FDG-PET
- Lumbar puncture
- Optional blood tests
- Single photon emission computed tomography (SPECT) (specify test/s)
- Optional neuropsychiatric testing
- Other tests

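### The exception to the prior-biomarker exclusion does not keep a previous amyloid scan out, so a Late-arm patient can be rated at week 12 with an amyloid PET result in use, against the comparator in the primary objective

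*Protocol*

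**What the plan says.** The exclusion criterion in Protocol section 7.4, repeated in the synopsis, covers a previous amyloid "imaging scan and/or has had other AD biomarker workup" (FDG-PET and/or CSF) before screening. The same bullet continues: "In some centres, the patient may receive a diagnostic workup before screening". It then adds: "These patients can be enrolled if the investigator is blind to the results until after randomization". The exception names no test, and the blind it requires ends once the patient is randomised.

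The related inclusion criterion in section 7.3 reads: "Patients should not have known amyloid status prior to randomization".

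Sections 6.1.1 and 9.4 state that in all arms, between baseline and week 12, each biomarker result that becomes available must go to the managing physician, and that the diagnosis and confidence are then collected at once. The only blind on test results after randomisation is in section 13.2. It applies to the Early arm, and only until that arm's PET result is available.

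The primary objective in section 5.4.1 compares the Early arm with "participants who have not yet undergone amyloid PET imaging". The Late arm is scanned at 8 months (± 8 weeks), well after the week-12 endpoint. The primary analysis uses the per-protocol set (section 12.2), which removes patients with relevant major protocol deviations and those lost to follow-up.

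**The concern.** The week-12 contrast is meant to set patients with an amyloid PET result against patients who have not been scanned. An eligibility rule that lets in someone already scanned, and seals the result only up to randomisation, allows a Late-arm patient to be on the wrong side of that contrast. Because the rule makes the patient eligible, enrolment is not a deviation and nothing in section 12.2 removes the patient on this ground. Such patients would pull the Late-arm rate towards the Early-arm rate, so the effect of early PET would be underestimated. The loss would fall mainly on the three stratum comparisons, which have the least power to spare.

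**Working it through.** **Tracing one patient through the text.** Take a patient who had an amyloid PET before screening, with the result still sealed.

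1. Section 7.4, exclusion: met, because there is a previous amyloid scan.
2. Section 7.4, exception: it can apply, because the patient was worked up before screening and the investigator is blind. No test type is carved out.
3. Section 7.3: passed, because amyloid status is not known before randomisation.
4. After randomisation to the Late arm: the required blind has ended. Section 13.2 does not extend it to this arm, and sections 6.1.1 and 9.4 call for the available result to be communicated before week 12.
5. Week 12: the patient is rated with an amyloid PET result in use and stays in the per-protocol set. Section 5.4.1 describes the comparator as not yet scanned.

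Steps 1 to 4 and step 5 cannot both be intended.

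**Reproducing the plan's power (section 12.7).** Inputs from the protocol: 300 per arm and 100 per arm per stratum; 10% withdrawal, so n = 300 × 0.9 = 270 and 100 × 0.9 = 90; difference d = 25 points; alpha .05 overall; Bonferroni over three strata, 0.05/3 (section 12.5.2). Assumptions: two-sided tests, and rates centred on 50%, because no base rate is given.

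The formula is the two-proportion power with continuity correction:

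- m = (n − 1/d)² / n
- z(power) = [d√m − z(1 − α/2) √(2p̄(1 − p̄))] / √(p₁(1 − p₁) + p₂(1 − p₂))

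Stratum: p₁ = 0.375, p₂ = 0.625, n = 90, z(1 − α/2) = 2.394.

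- m = (90 − 4)²/90 = 82.18
- z(power) = (0.25 × 9.065 − 2.394 × 0.7071)/0.6847 = 0.838, which gives 79.9%. The protocol states 80%.

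Overall, n = 270, alpha .05: above 99.9%, 99.6%, 92.7% and 61.0% at 25, 20, 15 and 10 points. The protocol states more than 99%, 99.6%, 93% and 61%. All the stated figures reproduce.

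**Illustrating the dilution.** Let f be the share of Late-arm patients with an earlier amyloid PET result in use at week 12, and assume they reach the Early-arm rate. The Late rate becomes p₁ + f·d, and the difference becomes d(1 − f). The protocol gives no f; 5% to 20% is an assumed range.

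Worked case, f = 10%: p₁ = 0.375 + 0.025 = 0.400, d = 0.225.

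- m = (90 − 4.444)²/90 = 81.33
- z(power) = (0.225 × 9.018 − 2.394 × 0.7069)/0.6887 = 0.489, which gives about 69%

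| f | Difference at planned 25 points | Stratum power | Overall power |
|---|---|---|---|
| 0 | 25.0 | 79.9% | >99.9% |
| 5% | 25 × 0.95 = 23.75 | 74.6% | >99% |
| 10% | 25 × 0.90 = 22.5 | about 69% | >99% |
| 20% | 25 × 0.80 = 20.0 | about 56% | 99.6% |

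**The case against.** The strongest reply is that the exception was never meant for amyloid scans. Section 7.4 uses two terms, an amyloid scan and other biomarker workup, and the exception speaks only of a workup. The cost rule in sections 10.1.2.3 and 12.6.1.3 for centres that work patients up before baseline, and the blind on other tests in section 13.2, both fit a reading in which the workup means FDG-PET and CSF. Section 6.1.1 also says amyloid PET is not reimbursed by most national health services, so routine workup would rarely include it. This stands as an account of likely intent and as a reason to expect few cases. It does not close the gap: the bullet opens with the amyloid scan, the exception carves nothing out, and at least eight centres must apply it alike.

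Two stronger readings should be resisted.

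- **CSF.** Section 5.3 states: "The ascertainment of brain amyloid can rely on PET with appropriate ligands or CSF assays". A reader might infer that a sealed CSF result damages the contrast in the same way. It does not. The objective contrasts having had amyloid PET with not having had it yet, not known with unknown amyloid status. Section 6.1.1 leaves usual investigations open, and Table 1 allows lumbar puncture at discretion through week 12. CSF therefore belongs to the intended comparator. Setting aside patients with a sealed CSF result would not isolate unknown amyloid status either, because other Late-arm patients may have a lumbar puncture after randomisation.
- **Section 9.2.** It begins: "For participants in the Late Amyloid PET and Free Choice arm, if results of any of the following tests are available at this visit". A reader might infer that a sealed amyloid scan is opened at the baseline visit. The list that follows does not name amyloid PET; only its catch-all for other tests could cover it. The point rests on sections 6.1.1 and 9.4 instead.

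**Conclusion.** The point holds as an inconsistency between the eligibility text and the primary objective. Read literally, sections 7.3 and 7.4 admit a Late-arm patient with an earlier amyloid PET, and sections 6.1.1 and 9.4 put that result in use before week 12.

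The size is unknown and probably small. The dilution d(1 − f) assumes that affected patients reach the full Early-arm rate. The range for f has no basis in the protocol, so the stratum figures show sensitivity and do not forecast a loss. A reader might infer that the primary comparison is underpowered; at the planned 25 points it is not, since overall power stays above 99% across the range. Nor does the protocol show that any such patients will be enrolled. What is at stake is chiefly the meaning of the Early-Late contrast and, second, the three stratum tests.

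**What to change.** In section 7.4 and the synopsis, limit the exception to FDG-PET and CSF workup, so that a previous amyloid scan excludes without exception. The eligibility text then agrees with the comparator in section 5.4.1, and f is zero for amyloid PET. No change to the sample size, the analysis sets or the tests is needed.

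The cost is one clause in two places. The downside is that a few patients with an earlier amyloid scan can no longer be enrolled. If they were never meant to be, the change only states the intent.

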## 7.5 Diagnostic Criteria

During screening, the following criteria will be used for giving patients a syndromic diagnosis of SCD Plus, MCI, and dementia where AD is in the differential diagnosis.

### 7.5.1 Subjective cognitive decline plus (SCD-Plus), modified from [\[Jessen et al, 2014\]](#)

Subjective cognitive decline (SCD) in individuals with unimpaired performance on cognitive test may represent the first symptomatic manifestation of Alzheimer's Disease (AD). The following list of features refers to SCD-Plus, in which the likelihood of the presence of preclinical AD is increased:

Inclusion criteria for SCD-Plus:

- The patient is  $\geq 60$  years old.
- The patient has perceived a decline in memory over time.
- The onset of the cognitive decline is within the previous 5 years and the duration is  $> 6$  months
- The Mini-Mental State Examination® (MMSE®) score is 27 to 30 out of 30.
- The clinical examination and neuropsychological assessment exclude MCI.
- Cognitive decline has been confirmed by an informant.
- The patient (or caregiver) has expressed concerns (worries) about the cognitive symptoms.

Exclusion criteria for SCD-Plus:

- Current or past psychiatric disorders according to ICD 10 (including major depression, anxiety disorder, substance-related disorders, schizophrenia, bipolar disorder, adult ADHD, post-traumatic stress disorder). However, a depressive episode, an anxiety disorder, or a substance-related disorder that occurred  $> 5$  years earlier and in no temporal association with the onset of SCD is not a criterion for exclusion.
- Current or past history of a neurologic disease with known potential impact on cognition.
- MRI lesions that would not be consistent with a diagnosis of AD.
- Current use of medication with known effect on cognition, including sedatives and drugs with anticholinergic effect, if the clinician believes that the use of those drugs is the cause of cognitive impairment.

## 7.5.2 Mild cognitive impairment (MCI) [\[Albert et al, 2011\]](#)

Diagnostic criteria for MCI are based on the National Institute on Aging and Alzheimer's Association (NIA-AA) Core Clinical Criteria:

- Concern regarding a change in cognition, as expressed by the patient, a proxy, or a physician.
- Impairment in one or more cognitive domains, as defined by neuropsychological test scores  $\geq 1.5$  SD below the age- and education-specific mean.
- Preservation of independence in functional abilities.
- No dementia.

## 7.5.3 Dementia where AD is in the differential diagnosis:

### 7.5.3.1 Probable AD dementia

The diagnostic criteria for probable AD dementia are based on the NIA-AA core clinical criteria in addition to the criteria for dementia [\[McKhann et al, 2011\]](#)

- Insidious onset
- Clear-cut history of worsening of cognition by report or observation
- The initial and most prominent cognitive deficits are evident on history and examination
- Presentation can be amnesic presentation or nonamnesic (language, visuospatial, executive function, etc)
- The diagnosis of probable AD dementia should not apply when there is evidence of substantial concomitant cerebrovascular disease, dementia with Lewy bodies, behavioural variant of frontotemporal dementia, semantic variant primary progressive aphasia or non-fluent/agrammatic variant primary progressive aphasia, evidence for another concurrent, active neurological disease, or non-neurological medical comorbidity or use of medication that could have a substantial effect on cognition.

### 7.5.3.2 Possible AD dementia

The diagnostic criteria for possible AD dementia are based on the NIA-AA core clinical criteria in addition to the criteria for dementia [\[McKhann et al, 2011\]](#):

- Atypical course (either a sudden onset of cognitive impairment or insufficient historical details or objective cognitive documentation of progressive decline.)

## 7.6 Withdrawal and Termination Criteria

### 7.6.1 Participant withdrawal

There are no formal withdrawal criteria for this study. During the conduct of the study, the Sponsor will review the safety data for trends and signals that would indicate the need for withdrawal of a participant.

In accordance with the Declaration of Helsinki, each participant is free to withdraw from the study at any time. Investigator(s) also have the right to withdraw participants from the study in the event of illness, adverse events (AEs), or other reasons concerning the health or well-being of the participant, or in the case of lack of co-operation.

Should a participant decide to withdraw after administration of the IMP(s), or should the investigator(s) decide to withdraw the participant, all efforts will be made to complete and report the observations up to the time of withdrawal as thoroughly as possible. A complete final evaluation at the time of the participant's withdrawal should be made and an explanation given of why the participant is withdrawing or being withdrawn from the study. The reason for withdrawal, if the participant will give one, must be noted in the electronic Case Report Form (eCRF). If the reason for withdrawal is a clinical AE, monitoring will continue until the outcome is evident. The specific event or test result(s) must be recorded in the eCRF.

#### **7.6.2 Replacement of participants withdrawn from the study**

Participants who are withdrawn will not be replaced.

#### **7.6.3 Premature termination of study or site**

There are no formal withdrawal or termination criteria for this study.

##### **7.6.3.1 Study termination**

##### **7.6.3.2 In case of premature termination or suspension of the study, the Sponsor will promptly inform the investigator, regulatory authorities, and independent ethics committees (IECs)/institutional review boards (IRBs) of the termination or suspension and the reason that this was deemed necessary. Site termination**

The study may be terminated at an individual centre if:

- The centre cannot comply with the requirements of the protocol.
- It is not possible for the centre to comply with Good Clinical Practice (GCP) standards.

## 8 TREATMENT OF PARTICIPANTS

### 8.1 Investigational Medicinal Products

The investigational products will be supplied by Piramal and GE Healthcare. Provision of Florbetaben and Flutemetamol will be under the responsibility of the drugs' contract manufacturers (on behalf of Piramal and GEHC), which will supply free doses for the study, as stated in the AMYPAD Grant Agreement (Description of Action).

